### Intervention and Comparator

Participants allocated to the intervention group will initially undergo screening by the Amazon Alexa device for symptoms of SARS-CoV-2 (screening questions in Table 1). All questions, excluding the first question to determine the preferred language, allow for the collection of responses that serve as epidemiological or clinical risk factors that predict the risk of having an infection with SARS-CoV-2. These participants will then undergo the same screening process, but by a trained research coordinator. Meanwhile, patients allocated initially to the comparator group will first undergo screening by a trained research coordinator, followed by digital screening by the Amazon Alexa device.

At the end of this process, all participants will undergo a postscreening survey (Table 2) conducted by a trained research coordinator. The goal of this postscreening survey is to evaluate user preference, concerns about privacy and data storage, and the Alexa software application engagement. The survey will ask 11 questions about their screening experience and their perception of voice-based technology. Questions 1, 2, and 6 allow specific evaluation for participants comfort with utilizing technology. More specifically, answers to these questions could serve as markers for the device’s perceived functionality and reliability as well as possibility for remote screening. Questions 3, 4, and 5 allow the collection of responses to assess the patient’s perception relative to data security. Questions 7 and 8 measure the participant’s subjective perception of the device’s effectiveness. Questions 9, 10, and 11 assess the overall ease of use of the device.

Other variables will be collected in the postscreening phase of the study such as SARS-CoV-2 vaccine status, assigned sex at birth, and duration of digital screening. These variables will be utilized for stratification-based statistical analysis on the answers obtained in the postscreening survey.

Prespecified subgroups of interest include those by language (French and English), sex, and age.

**Table 2 table2:** Postscreening survey questionnaire.

Postscreening survey questions	Response type
1. Did you feel comfortable speaking into the Amazon Alexa device?	5-point Likert scale
2. Have you used this type of device before or do you own this type of device?	Binary mode
3. Would you feel comfortable being screened for symptoms using the Amazon Alexa device?	Binary mode
4. Do you have any concerns about privacy or data safety?	5-point Likert scale
5. Do you feel your data would be kept secure by such a device?	5-point Likert scale
6. Can you see yourself using such a device at home to assist with any healthcare needs?	5-point Likert scale
7. Did you feel the check-in asked the screening questions appropriately?	5-point Likert scale
8. Did you feel the check-in minimized your chance of contracting COVID-19?	5-point Likert scale
9. Was the language easy to understand?	5-point Likert scale
10. Was the check-in easy to use?	5-point Likert scale
11. How would you rate this check-in overall?	5-point Likert scale

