### Outcome Measures

The primary outcome of the study will be the concordance of screening for symptoms of SARS-CoV-2 carried out by the Amazon Alexa device compared with the manual screening carried out by a trained research coordinator. The secondary outcome will be a 5-point Likert scale and binary mode responses evaluating patients’ perceived comfort interacting with Alexa. The above outcomes will be measured as part of the postscreening survey carried out by the research coordinator at the end of the SARS-CoV-2 symptom-screening process and inputted into a secure web application form. The ease of the Amazon Alexa screening process, privacy and data safety concerns, interest in digital health care at home, and willingness to be vaccinated will be asked with a standard 5-point Likert scale. The relationship between the participant’s vaccine status and the answers regarding the participant’s comfort with digital health use, as well as the relationship between interest in voice response systems use at home and cohort demographics (eg, gender, age, and relevant medical history) will be determined by a linear regression model. Finally, any technical issues will be noted manually, on the REDCap platform, as well as any comments, remarks, and questions made by the research participants. These notes will be taken into consideration in the evaluation of the efficiency and accessibility of the digital Amazon screening. However, it is important to note that given that the survey questions are clear and objective, there is little risk of bias that in-person observations will affect the internal validity of the study’s results.

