### Statistical Analysis

The coprimary end points for this study relate to the IRR on the accuracy of the randomized screening data from Amazon Alexa compared to coordinator data as the comparator. IRR will be evaluated using simple and weighted Cohen κ statistics (where possible) and percentage concordance between responses obtained from Amazon Alexa and research coordinators. The calculated κ scores will be compared between the 2 study arms for each screening question. In addition, linear mixed-effects model will be used to investigate differences in the 2 study arms, adjusting for the fixed effect of the screening order and the random effect of correlated observations in the demographic data. Furthermore, postscreening survey questions will be examined and presented on a Likert scale. This study will aim to recruit at least 52 participants, with minimally 26 participants in each study arm. The estimation of the sample size is based on the *kappaSize* package in R (version 4.1.2; R Foundation for Statistical Computing), with a 1-tailed test null κ score of 0.6 assuming a proportion of positive ratings of 0.9 and a preliminary κ score of 0.9 [13,14]. The sample size will also be adjusted with the power analysis of one-way ANOVA and the chi-square test to obtain a power of 0.8, accounting for a large effect size of above 0.4 and a significance level of .05. The demographic data will be presented in the baseline characteristics table, with categorical variables as counts (percentages) and continuous variables as medians and interquartile ranges.

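### The survey analyses that the protocol names leave out the randomised screening order, and one named stratifier, duration of the Alexa session, may itself depend on that order

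*Protocol article*

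**What the plan says.** Under Randomization and Blinding, the protocol article randomises participants 1:1 to begin with Alexa or with the coordinator, and gives priming as the reason. Under Intervention and Comparator, the comparator group "will first undergo screening by a trained research coordinator, followed by digital screening by the Amazon Alexa device". Both screenings use the same questions. Everyone is then surveyed once, by a coordinator, after both screenings.

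The article describes the survey analysis in four places:

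- **Stratifiers** (Intervention and Comparator): variables "such as SARS-CoV-2 vaccine status, assigned sex at birth, and duration of digital screening", followed by "These variables will be utilized for stratification-based statistical analysis on the answers obtained in the postscreening survey".
- **Subgroups** (same section): "Prespecified subgroups of interest include those by language (French and English), sex, and age".
- **Regressions** (Outcome Measures): comfort with digital health against vaccine status, and interest in home use against "cohort demographics (eg, gender, age, and relevant medical history) will be determined by a linear regression model".
- **Presentation** (Statistical Analysis): "postscreening survey questions will be examined and presented on a Likert scale".

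Order appears in one model, under Statistical Analysis: a "linear mixed-effects model will be used to investigate differences in the 2 study arms, adjusting for the fixed effect of the screening order". The response variable of that model is not given.

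**The concern.** The protocol treats order as important enough to randomise, and it plans to compare kappa between the two arms. Where it lists the factors for the survey, order is absent. Yet rehearsing the questions with a person could plausibly change how easy or comfortable Alexa then seems.

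Two things are at stake. First, an overall survey average describes a mixture of people who met Alexa prepared and people who did not, and nothing in the stated survey analysis would show whether they differ. Second, duration of the Alexa session is an outcome of the session and not a baseline trait. If rehearsal changes both the duration and the rating, strata of duration partly sort participants by arm, and a link between short sessions and high ratings could be mistaken for something about the device or the user.

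**Working it through.** **Inputs from the protocol article.** Total sample 52, at least 26 per arm; 1:1 allocation; significance level .05, power 0.8 and a large effect size of above 0.4 for the ANOVA and chi-square calculations (Statistical Analysis).

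**Inputs not in the protocol (assumed).** Likert SD 0.8 to 1.2; any rehearsal effect on ratings or on duration.

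**1. The plan's own figure.** A two-group one-way ANOVA with f = 0.4, alpha .05 and power 0.8 needs a total of 51.05, so 26 per group and 52 in all. This reproduces the stated size. The kappa inputs also give 52 when read as an expected one-sided 95% lower limit of 0.6: 2.7055 / 0.05273 = 51.3. Reporting the survey by order changes neither calculation.

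**2. Where order is named.**

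| Stated survey analysis | Factors named | Order named? |
|---|---|---|
| Stratification | vaccine status, sex, duration of digital screening | no |
| Subgroups | language, sex, age | no |
| Linear regressions | vaccine status; gender, age, medical history | no |
| Likert presentation | none | no |
| Mixed-effects model | arm, screening order | yes, but response not given |

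**3. What an overall mean represents.** With equal arms and an order effect of D points, the all-participant mean differs from the Alexa-first mean by D/2. For illustration, D = 0.5 gives 0.25 point. At SD 1 the standard error of the overall mean is 1/√52 = 0.139, so the gap is 0.25/0.139 = 1.8 standard errors. D could be zero or of either sign.

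**4. Precision of an order comparison.** The 95% half-width is t(0.975, 50 df) × SD × √(2/26) = 2.009 × SD × 0.277:

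- SD 0.8: 0.45 point
- SD 1.0: 0.56 point
- SD 1.2: 0.67 point

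The detectable standardised difference at 80% power (two-sided .05) is d = 0.79. Power is 81% at d = 0.8 (equivalent to f = 0.4 with two equal groups), 42% at d = 0.5 and 19% at d = 0.3.

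**5. Duration and rating.** Suppose order shifts duration by d1 and rating by d2, in within-arm SD units, and the two are unrelated within arm. The absolute correlation across all participants is then

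0.25·d1·d2 / √[(1 + 0.25·d1²)(1 + 0.25·d2²)].

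- d1 = d2 = 0.5: 0.0625/1.0625 = 0.06
- d1 = d2 = 1: 0.25/1.25 = 0.20

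For scale, significance at n = 52 needs a correlation of about 2.009/√(2.009² + 50) = 0.27. Order alone, under these assumed shifts, would produce a weak association.

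**6. The other factors.** Sex, age, language and vaccine status are participant characteristics that the order of screening does not alter. Randomisation balances order across them on average, so averaging over order does not confound those comparisons.

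**The case against.** The strongest reply is that the text is silent on order and does not exclude it.

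- A reader might infer that the ratings are pooled across arms. No sentence says so. The Likert statement specifies neither pooling nor analysis by arm.
- The stratifier list is open-ended and describes variables collected after screening. Allocation is fixed before screening and would not naturally appear there.
- The mixed model includes order and names no response, so it may cover survey scores. Its position, ahead of a separate sentence about the survey, suggests screening data but does not settle the matter. A reader who concludes that the randomised comparison goes unused for the survey is going beyond the text.
- Tabulating a secondary survey by arm is often left to a full protocol or analysis plan, and neither is at hand.
- Everyone is surveyed after both screenings. A reader might take the Alexa-first arm as the estimate for standalone or home use, but those participants have also been screened by a coordinator before they give ratings.
- Several survey items, such as prior device use and data security, have little evident link to rehearsal.

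All of this stands, and it limits the point. It does not remove it. The article does list factors for the survey in three places without the randomised one, and it does choose a stratifier measured after randomisation. It also leaves unclear whether its only model with order applies to the survey.

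**Conclusion.** The point holds in a limited form. The survey analyses as named omit screening order, and duration of digital screening is a post-randomisation variable whose association with ratings could partly reflect order. Under assumed shifts of 0.5 to 1 SD in both, that contribution is a correlation of about 0.06 to 0.20. An overall mean would differ from the Alexa-first mean by half of whatever order effect exists; the protocol gives no figure for that effect, its direction or the SD.

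The documents do not support a claim that the comparisons by sex, age, language or vaccine status are biased. The sample size is unaffected. This is a useful clarification of a secondary analysis and does not threaten the primary result.

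**What to change.** State in the analysis plan that:

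1. each Table 2 item and the digital-session duration are reported by randomised order, with the between-order difference and its 95% confidence interval;
2. order is a term in the survey regressions;
3. the association of duration with ratings is examined within order;
4. the mixed-effects model does, or does not, take survey scores as a response.

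Keep the all-participant figures beside the by-order results, and do not label the Alexa-first arm as standalone use.

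The cost is wording and a little more analysis. Randomisation is already recorded in REDCap and no more participants are needed. The main limitation is low power for modest order effects (42% at d = 0.5), so the interval should be read and a non-significant difference should not be taken as evidence of no order effect.

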## Results

Funding for the VOICE-COVID-19-II trial was obtained in May 2021. The recruitment of participants for the VOICE-COVID-19-II trial started in May 2021, with simultaneous acquisition of data by the Amazon Echo Show 8 device, and is expected to be completed in fall 2022. Data analysis is expected to be completed in early 2023. Subsequently, trial results and analysis are expected to be published by mid-2023.

## Discussion

### Expected Findings

The study aims to test the concordance of screening for symptoms of SARS-CoV-2 done by Amazon Alexa compared to manual screening done by research coordinators. It also aims to evaluate the perceived comfort of patients when interacting with Alexa. Voice-based technology has the potential to improve clinical treatment for patients affected by SARS-CoV-2 by optimizing rapid and accurate data acquisition and can be extended to allow for screening of other conditions. Before implementing this interactive voice response system, the IRR of the program screening for the virus and overall patient experience, compared to the standard person-to-person screening, must be evaluated.

With standard methods of screening for symptoms and exposures, there is an increased burden on health care professionals that remains strenuous in the context of the pandemic. The use of commercially available digital tools to aid in screening for SARS-CoV-2 symptoms may be instrumental in reducing the burden on health care personnel, as well as minimizing opportunistic spread of disease via person-to-person contact [15].

A number of approaches using available digital health technologies to screen for SARS-CoV-2 symptoms are being explored, including automated text messaging and smartphone apps [16,17]. However, interactive voice response systems remain relatively unexplored. A previous study has evaluated the quality of health information dissemination on cancer screening provided by voice assistants, such as Siri, Alexa, and Cortana, but did not evaluate these devices’ ability to screen for cancer [18]. One study evaluated the quality of speech intelligibility of Amazon Alexa and Google Home by providing individuals with intellectual disabilities with smart speaker devices [19]. Another recent study screened patients with major depressive disorder with the Patient Health Questionnaire 9 via randomizing screening with Amazon Alexa compared to manual screening [20]. However, manual screening was done through paper format, and the time between digital and manual screening was 1 month. The potential ease of use of voice-based commands, which, when optimized, would better simulate standard person-to-person interactions compared to requiring digital input, could prove to be optimal in situations where the use of electronic recording of data may be difficult, such as with older participants. Furthermore, the use of Amazon Alexa, a voice response system available at home and other nonclinical environments, could provide additional advantages in terms of remote data collection. A reliable method of rapid acquisition of medical data easily accessible to patients could significantly facilitate future trials and personalizing health care delivery. Similar to other remote digital technology, such as Google Home or Apple’s Siri, voice response systems have potential for great scalability for larger participant numbers, given its commercial nature, cloud-based data collection, and easy access.

However, the increasing popularity of remote screening tools during the SARS-CoV-2 pandemic revealed a need for objective measures of the reliability of the data acquired by these tools. In particular, the previous phase of this study did not directly address the risk of bias in the virtual screening question answers when presented with the comparator set of in-person questions beforehand. The strengths of this study are founded upon its design to isolate a verified measure of the accuracy of the screening method and the use of commercial interactive voice response systems. This study aims to examine the reliability of the data acquired by the device while accounting for the priming bias inherent in previous similar studies, where participants would be affected by choices presented by the in-person set of screening questions used as the comparator. In addition, the Amazon Alexa program used in the skill set is based on a widely accessible commercial device designed for home use, which would provide a reasonable simulation of the technology that would be used for widespread public screening.

### Limitations

The study does have some limitations. Although the sample size may be adequate in detecting IRR between the virtual screening program and the standard in-person screening questionnaire, it is too small to detect the effectiveness of the questionnaire in triaging patients exposed to COVID-19. While the use a more extensive COVID-19 questionnaire may have increased the amount of data available for analysis, a shorter questionnaire developed with clinical experts was used to enhance patient recruitment. Given that the focus of this study was the accuracy of information obtained remotely compared to an in-person standard and not specifically to screen for SARS-CoV-2, insight into its capability as a screening measure was limited. However, regarding the diagnostic and screening accuracy of voice-based digital screening for COVID-19, a larger-scale study utilizing gold standard diagnostic assays (ie, reverse transcription polymerase chain reaction) would be required. Should a survey evaluating the accuracy of the questionnaire itself be proven to be effective, interactive voice response systems, such as Amazon Alexa, could provide users with a notification for their risk of a positive diagnosis and whether testing is encouraged given a posttest likelihood of illness.

In terms of the questionnaire, it is possible that some questions regarding personal contact with COVID-19 will have some interperson variability secondary to question interpretation. However, given the objective nature of the COVID-19 questionnaire as well as individuals’ lived experiences with the pandemic, the overall potential for risk of bias is low. Furthermore, although the study and questionnaire used are limited to recording answers in a 5-point Likert scale and a binary response of yes or no, speech AI is becoming increasingly sophisticated, with improved speech recognition and more flexible conversations in newly developing propriety speech AI. This could prove to be a unique strength of voice-based screening in future health care delivery, with a possibility of more personalized interactions with patients, nuanced screening questions, and more efficient information dissemination to patients in the form of an interactive question-and-answer program. As remote data collection develops over time, there will be new potential avenues of medical AI research for personalized health care delivery with intelligent voice-based assistants.

### Conclusion

In conclusion, the second phase of the VOICE-COVID-19-II randomized controlled trial aims to evaluate the accuracy of data capture by interactive voice response systems, such as Amazon Alexa, compared to health care providers as the baseline. If the study proves to be effective, it could open additional avenues of research and would provide a novel viewpoint on implementing digital health in the context of the pandemic, allowing for screening in both hospitals and at home.

## Appendix

Multimedia Appendix 1 Standard Protocol Items: Recommendations for Interventional Trials (SPIRIT) checklist.

## Abbreviations

AI: artificial intelligence
ASR: automatic speech recognition
HF: heart failure
IRR: interrater reliability
MUHC: McGill University Health Center
NLU: natural language understanding
REDCap: Research Electronic Data Capture
REB: Research Ethics Board
RVH: Royal Victoria Hospital
UPS: uninterrupted power supply
